**Study Protocol for the Real-world E-Consumer Cohort of pre-exposure prophylaxis (RECOPE) in China**

1. **Rationale of the study**

HIV/AIDS remains a major public health challenge in China and worldwide. According to the Joint United Nations Programme on HIV/AIDS (UNAIDS), 39.9 million people are living with HIV globally in 2023, with approximately 1.5 million new infections reported that year [1]. In China, over 1.2 million individuals were living with HIV by the end of 2022, and more than 107,000 new infections were reported in the same year [2]. The epidemic continues to disproportionately affect vulnerable populations such as men who have sex with men (MSM) and sex workers.

Pre-exposure prophylaxis (PrEP) is a proven biomedical prevention tool that reduces the risk of HIV acquisition through sexual contact by up to 99% when taken correctly [3]. Two main PrEP regimens are available: (1) the daily regimen, recommended for all high-risk populations, which involves taking one pill daily; and (2) the event-driven (ED) regimen, also known as “2-1-1,” recommended for MSM, which involves 2 pills 2–24 hours before sex, followed by 1 pill 24 hours and 48 hours later. The World Health Organization and Chinese Expert Consensus both strongly recommend PrEP for individuals at high risk of HIV[4,5]. PrEP is officially approved in China in 2020, marking an important step toward HIV prevention scale-up.

With the rapid development of internet hospitals and online health platforms, new pathways for PrEP access have emerged. Online platforms offer discreet and convenient services, reducing barriers related to stigma and healthcare access. For MSM and other key populations, online purchase of PrEP may overcome barriers encountered in traditional clinic settings. However, unlike face-to-face clinical services, online platforms may lack structured mechanisms for adherence counseling and follow-up.

In China, BluedHealth, a leading internet-based health platform, has become a major channel for PrEP distribution. In 2023, BluedHealth reported an average of over 3,000 PrEP sales per month, reflecting increasing acceptance of online PrEP services. Despite this expansion, there is little evidence regarding adherence patterns and associated factors among real-world online PrEP consumers in China[6].

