**3.2 Sample Size Calculation**

The required sample size is calculated using Cochran’s formula for estimating a single population proportion, incorporating finite population correction and a design effect adjustment, as shown in Equation (1). Based on previous studies, we assumed an optimal adherence prevalence of 60%, a two-sided significance level of α = 0.05, and a desired precision (margin of error) of 5%.

A design effect (deff) is included to account for potential clustering introduced by the recruitment workflow, since participants will be conveniently recruited by the designated recruiters through the same platform channels may share unobserved similarities. Following the standard formula deff = 1 + (m – 1) × ICC, we assumed an average cluster size of approximately 11 participants per recruiter and a small intraclass correlation coefficient (ICC) of 0.01. This yielded deff ≈ 1.1, which is applied as a conservative adjustment [7,8].

In addition, a 15% anticipated loss to follow-up is included. The final minimum required sample size is calculated to be 424 participants using PASS software.

n = deff × [N p̂ q̂] / [(d² / 1.96²)(N – 1) + p̂ q̂] (1)

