**Other measures**

***Demographic characteristics***

The participants will be asked about their age (in years), sex (male, female), ethnicity (Han, others), employment status (students, unemployed, employed), education level (Junior high school or below, senior high school or equivalent, bachelor degree or equivalent, master degree or above), marital status (married/living with a partner, unmarried/divorced/separated/widowed), and monthly income (≤3000, 3001-5000, 5001-7000, 7001-10000, 10001-15000, 15001-20000, >20000 CNY). Income is further recoded into a binary variable using 3000 CNY (approximately 700 USD) as a threshold as it is the national average monthly income in China.

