**Regression Analyses**

**Event-driven (ED) users:** Three regression models will be fitted:

- Model 1: A univariable and multivariable generalized linear mixed model (GLMM) with a logit link and random intercept to evaluate factors associated with past three-month adherence using data from baseline, 3-month, and 6-month visits. In the multivariable GLMM, all the exposure variables of interest will be involved.
- Model 2: A univariable and multivariable GLMM with the same structure to evaluate factors associated with past one-month adherence using data from baseline and all follow-up visits.
- Model 3: A logistic regression model for consistent adherence, defined using data from the 3- and 6-month follow-ups, with baseline socio-demographics and averaged time-varying covariates included as independent variables.

**Daily users:** Regression analysis is planned only for past one-month adherence (Model 2), using a GLMM with the same structure as for ED users.

All models will include fixed effects for exposure variables of interest. Univariable GLMMs will be fitted first to estimate crude odds ratios (ORs) and 95% confidence intervals (CIs) for each covariate. Multivariable GLMMs will then be fitted including all pre-specified, theory-driven covariates—regardless of their univariable associations—to estimate independent effects while adjusting for potential confounding.

Missing data will be handled under a complete case framework. Specifically, missing data are expected to arise primarily from loss to follow-up. No imputation will be performed. GLMM models inherently allow for unbalanced data across repeated measures, and participants with incomplete follow-up will contribute all available observations. Attrition patterns will be described in supplementary analyses.

All analyses will be performed using R (version 4.4.2). Statistical significance will be defined as a two-sided p-value < 0.05.

1. **Ethics and Confidentiality**

The study protocol will be reviewed and approved by the Institutional Review Board of Tsinghua University. All procedures will be conducted in accordance with the ethical standards of the Declaration of Helsinki and relevant national guidelines.

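### Model 3 may carry up to about 21 terms on few events per term, so ordinary logistic regression risks odds ratios biased away from 1; Firth penalised fitting is a cheap remedy

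*Protocol*

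**What the plan says.** Protocol Section 3.8 (Regression Analyses) plans three models for ED users. Models 1 and 2 are logistic mixed models on repeated visits. Model 3 is a logistic regression of consistent adherence, which Section 3.6 defines as optimal past 3-month adherence at both the 3- and 6-month surveys, so each ED user contributes one record.

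Covariates are described in three places:

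- For Model 1: "In the multivariable GLMM, all the exposure variables of interest will be involved".
- For Model 3: socio-demographics from baseline, plus time-varying covariates averaged over visits.
- For all models: fixed effects for the exposures of interest. The multivariable mixed models keep every pre-specified covariate whatever its univariable result.

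No explicit covariate list is given. Section 3.6 defines the measured variables, for example "sex (male, female), ethnicity (Han, others), employment status (students, unemployed, employed". Missing data are handled by complete cases, and ED users who report no sex or never started PrEP have a missing outcome.

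Section 3.2 sizes the study for a single proportion in both regimens together: "we assumed an optimal adherence prevalence of 60%, a two-sided significance level of α = 0.05", with "a desired precision (margin of error) of 5" percent. The result: "The final minimum required sample size is calculated to be 424 participants using PASS software". Section 3.4 separately uses 650 enrolled as a recruitment threshold.

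**The concern.** Identifying factors associated with adherence is part of the primary objective, and the adjusted odds ratios are what serve it. The sample size calculation covers neither the regressions nor either regimen alone. Model 3 loses participants four times: to attrition, to the split by regimen, to the missing-outcome rule for those without sex, and to the need for outcomes at two visits. It has no repeated rows to compensate.

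With few events per term, maximum-likelihood logistic regression biases log odds ratios away from zero. It can also give infinite or unstable estimates where a category is nearly empty. Section 1 notes that the ED regimen is recommended for men who have sex with men, yet sex is a listed covariate, so the ED group may contain very few women. Overstated associations would feed into the interventions the study is meant to inform.

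**Working it through.** **1. The plan's own figure.** The design effect is 1 + (11 - 1) x 0.01 = 1.10, in line with "This yielded deff ≈ 1.1, which is applied as a conservative adjustment". Section 3.2 does not give N for Equation (1). Section 1 says "In 2023, BluedHealth reported an average of over 3,000 PrEP sales per month", so N is taken as about 2,900 to 3,000 (assumption).

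- N = 2,900: 1.1 x 2,900 x 0.24 / [(0.0025/3.8416) x 2,899 + 0.24] = 765.6 / 2.1266 = 360.0. Then 360.0 / 0.85 = 423.5, rounded up to **424**.
- N = 3,000: 361.4, then 426.

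So 424 reproduces, with "a 15% anticipated loss to follow-up is included", and leaves 424 x 0.85 = 360 participants of both regimens.

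**2. Terms, if every variable of Section 3.6 enters as coded.**

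| Block | Terms |
|---|---|
| Age 1, sex 1, ethnicity 1, employment 2, education 3, marital status 1, binary income 1 | 10 |
| Chemsex 1, partners 1, commercial sex 1, role 2, condom use 1 | 6 |
| Dosing knowledge 1, stigma 1 | 2 |
| Self-efficacy 1, PHQ-9 1, resilience 1 | 3 |
| **Total** | **21** |

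**3. Ceiling.** Events are counted in the rarer outcome class. With every participant on ED, no missing outcome and a 50/50 split: 360 x 0.5 / 21 = **8.6 per term**. No ED share can raise this at 424 enrolled with 21 terms.

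**4. Plausible range.** None of these inputs is in the protocol; all are assumed.

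- ED share: 50-70%.
- Sexually active in both windows: 80-90%.
- Consistent adherence: 36-48%. With 60% at each visit, independent visits give 0.6 x 0.6 = 0.36; a within-person correlation of 0.5 gives 0.36 + 0.5 x 0.24 = 0.48.

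| Enrolled | Low end | High end |
|---|---|---|
| 424 | 360 x 0.5 x 0.8 = 144; x 0.36 = 52; /21 = **2.5** | 360 x 0.7 x 0.9 = 227; x 0.48 = 109; /21 = **5.2** |
| 650 | 552.5 x 0.5 x 0.8 = 221; x 0.36 = 80; /21 = **3.8** | 552.5 x 0.7 x 0.9 = 348; x 0.48 = 167; /21 = **8.0** |

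**5. Fewer terms.** Leave out the three factors not named in the primary objective (resilience, commercial sex, knowledge), sex, and one of the two role terms: 21 - 5 = 16. At 424 the range becomes 52/16 = 3.3 to 109/16 = 6.8.

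**6. Consequence, by simulation.** All category frequencies are assumed. The first simulation used 1,000 data sets per row, 21 terms and a true odds ratio of 1.5 for self-efficacy, with 2% women, 4% lowest education and 8% non-Han:

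| Events per term | Mean inflation of log OR | Data sets with an inestimable term |
|---|---|---|
| 2.5 | 25% | 61% |
| 3.1 | 18% | 46% |
| 4.8 | 14% | 20% |
| 7.4 | 7% | 6% |

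Two further simulations compared maximum likelihood with Firth's method:

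- n = 145-225, 400 runs each, 3% women: log ORs inflated by 11-23% (a true 1.60 became 1.69-1.77), and an inestimable or diverging term in 9-38% of data sets. With Firth, bias was within about 8%, and the self-efficacy RMSE fell from 0.30 to 0.24 (n = 145) and from 0.20 to 0.17 (n = 225).
- The other gave 12-22% inflation at 2.5-5 events per term and 7-9% near 8, with an inestimable term in 7-35% and 1-2% of data sets. With Firth, bias was within about 4%, with lower RMSE throughout.

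**The case against.** **The full-entry wording belongs to the mixed models.** This stands. The quoted sentence describes Model 1, and the rule of keeping covariates whatever their univariable result is also written for the mixed models. A reader might infer that the protocol forces exactly 21 terms into Model 3. It does not: there is no list, and role averaged over visits need not remain two terms. Hence up to about 21; step 5 shows that 16 terms do not remove the problem.

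**The range rests on unstated inputs.** This also stands. Only the ceiling is free of the ED share. Recruitment may reach 650, where the problem is milder.

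**Inflated or inestimable odds ratios are not a foregone conclusion.** A reader might infer that they are. The share of data sets with an inestimable term moves widely with the assumed frequencies of rare levels, and those levels are mostly demographic adjusters. The bias is also smaller than the sampling error: 1.60 becoming 1.69-1.77 is 0.05-0.10 on the log scale, against an RMSE of 0.20-0.30.

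**The mixed models are a different case.** A reader might extend the point to every multivariable model, including the daily-user one. At 50-80% ED, Model 1 has about 10-16 rarer-class observations per term (3.4-5.5 counting each person once). The daily-user model, at 20-50% daily, has about 5-14 (1.4-3.4 by person). These observations are correlated within person, but no mixed model was simulated, so the claim is not made there.

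**The estimator could be left to a fuller SAP.** Possibly, and if one specifies penalised fitting, the point falls. But Section 3.8 presents itself as the pre-specified plan and fixes a logistic regression without a penalty, so ordinary maximum likelihood is the natural reading. Keeping pre-specified covariates is sound and is not criticised here.

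**Conclusion.** The point holds for Model 3, as a risk and as a cheap improvement. With up to about 21 terms it cannot exceed 8.6 events per term at 424 enrolled. Under the stated assumptions it has about 2.5-5, or about 4-8 with 650 enrolled. Ordinary maximum likelihood then risks log odds ratios biased away from zero by roughly 10-20%, somewhat more at the sparsest end and about 7-9% near 8 events per term. Coefficients for sparse categories may be inestimable; how often depends on frequencies that the protocol does not give. The sample size itself is not shown to be wrong for its stated purpose, since 424 reproduces as a precision calculation for one proportion.

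**What to change.** In Section 3.8, state that Model 3 will be fitted by Firth penalised logistic regression with profile-likelihood confidence intervals, keeping the pre-specified covariates.

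The cost is a sentence of protocol wording. Standard R packages do this, and no extra participants or data are needed. The downside is a less familiar estimator with slight shrinkage. Firth's method gives finite estimates under separation, but cannot estimate a category that no one in the analysed set occupies. Nothing calculated here supports a particular rule for collapsing education or dropping sex, or a penalty on the mixed models, so none is proposed.

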**Primary Outcome**

The primary outcome of this study is PrEP adherence, assessed separately for daily and event-driven (ED) regimen users at each follow-up visit (1, 3, and 6 months after baseline).

- **ED users:** Adherence to ED regimen is assessed by four items. First, the participants are asked whether they had engaged in sexual activity in the past one and three months, respectively (the 1-month follow-up survey only asked this question for the past one month). Those who answer “no” or reported to have never initiated PrEP in a previous question were treated as missing data for PrEP adherence. Those who answer “yes” are then asked if they had taken PrEP for each sexual encounter in the corresponding time period, including those with both primary (e.g., main or long-term partners) and non-primary (e.g., casual or commercial partners) sexual partners (1 = every time, 2 = sometimes, and 3 = never). The participants who choose “every time” or “sometimes” are subsequently asked three adherence questions based on the ‘2-1-1’ dosing guideline: (i) whether (yes or no) they took two pills of PrEP 2 to 24 hours before the sexual activity for each medication (timepoint A); (ii) whether they took one pill 24 hours after the first dose for each medication (timepoint B); and (iii) whether they took another pill 48 hours after the first dose for each medication (timepoint C). The participants who reported to take PrEP for each sexual encounter and chose “yes” to all three adherence questions are classified as “being adherent,” otherwise, they would be classified as “non-adherent.” Lastly, three binary outcome variables are constructed: past 1-month adherence based on baseline and all follow-up data, past 3-month adherence based on baseline and 3- and 6-months follow-up data, and consistent adherence based on 3- and 6-months follow-up data (defined as having optimal past 3-month adherence at both 3- and 6-month follow-up surveys).
- **Daily users:** Adherence to daily PrEP regimen is assessed with a single item: “In the past month, have you ever failed to take PrEP on time and in a correct dosage? (yes/no).” Participants who answer “no” are classified as “adherent,” and those who chose “yes” are categorized as “non-adherent”

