***Social-psychological variables***

Self-efficacy of keeping optimal PrEP adherence is evaluated by an adapted version of the Condom Use Self-Efficacy Scale [10], which has been validated among Chinese MSM populations [11]. The adapted scale included six items related to consistent PrEP use (e.g., “Even if my sexual partner is unwilling, I am confident in continuing PrEP use”). Each item is rated on a 5-point Likert scale, ranging from 1 (strongly disagree) to 5 (strongly agree). A summative score ranging from 6 to 30 is created by adding up the score of each item, with a higher total score indicating greater self-efficacy in adhering to PrEP.

Depressive symptoms are assessed by the Patient Health Questionnaire-9 (PHQ-9) [12], which has been validated in Chinese MSM populations and demonstrated strong psychometric properties [13]. The questionnaire asked participants about the frequency of specific symptoms experienced over the past two weeks, with each item rated on a 4-point Likert scale ranging from 0 (not at all) to 3 (nearly every day). A summative score ranging from 0 to 27 is created by adding up the score of each item.

Psychological resilience is measured by the 2-item Connor-Davidson Resilience Scale (CD-RISC-2) [14], which has been validated among MSM populations [15]. The items included “Able to adapt to change” and “Tend to bounce back after illness or hardship”. Responses are rated on a 5-point Likert scale ranging from 0 (never) to 4 (always). A summative score ranging from 0 to 8 is created by adding up the scores of 2 items.

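### Models 1 to 3 never relate an earlier psychosocial score to later adherence, so an effect of adherence on the score cannot be excluded

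*Protocol*

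**What the plan says.** **Outcome (3.6, Primary Outcome).** Adherence looks back from the survey. ED users are asked "whether they had engaged in sexual activity in the past one and three months, respectively", and the dosing questions refer to the same periods. The daily item reads "In the past month, have you ever failed to take PrEP on time and in a correct dosage". Consistent adherence is "defined as having optimal past 3-month adherence at both 3- and 6-month follow-up surveys".

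**Scores (3.6, PrEP-related and Social-psychological variables).** Self-efficacy is agreement with statements such as "Even if my sexual partner is unwilling, I am confident in continuing PrEP use", which is confidence on the survey day. The PHQ-9 asks about "the frequency of specific symptoms experienced over the past two weeks". No recall period is given for the stigma and resilience scales.

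**Models (3.8, Regression Analyses).** Model 1 is a random-intercept logistic model "to evaluate factors associated with past three-month adherence using data from baseline, 3-month, and 6-month visits". Model 2 has the same structure for past-month adherence at baseline and every follow-up, for ED and daily users. Model 3 is a logistic regression for consistent adherence in ED users, "with baseline socio-demographics and averaged time-varying covariates included as independent variables". No lag between score and outcome is stated for any model.

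**Interpretation.** Section 3.8 says the multivariable models estimate independent effects. The primary objective asks for factors associated with adherence, names self-efficacy first among the psycho-behavioral ones, and wants evidence to inform interventions. The limitations cover selection, recall, social desirability, monitoring and omitted factors. They do not mention reverse direction.

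**The concern.** A person who has just missed doses may rate their confidence in adhering lower, or report lower mood. If the score is taken when the recall window closes, this produces an association even when the score has no influence on later adherence. A random intercept does not remove it, because the feedback acts within a person from visit to visit.

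What is at stake is the direction of the relation. If self-efficacy follows adherence, an intervention to raise it need not improve adherence. A cohort with surveys at 0, 1, 3 and 6 months could examine which comes first, but none of the planned models does so.

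**Working it through.** **1. Timing, model by model.**
- Model 1, baseline row: the outcome covers the three months before baseline. No earlier survey exists, so the score must come from the end of that window.
- Model 1, months 3 and 6, and all follow-up rows of Model 2: no lag is stated, so same-visit pairing is the plain reading, though it is inferred. Self-efficacy is then measured as the window closes, and the PHQ-9 covers the last 2 of about 4 or 13 weeks.
- Model 3: the outcome covers months 0-3 and 3-6. A 6-month score would follow both windows. A 3-month score follows the first and precedes the second. Baseline scores precede both. The waves averaged are not named, so the mean may mix before and after.

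**2. Size if feedback exists.** The plan gives no figure to reproduce here, so the check is a simulation. Inputs from the protocol (3.2): adherence about 60%, and 424 × 0.85 = 360 participants. Assumed: all 360 contribute (the ED share is not given), waves at 0, 3 and 6 months, no effect of the score on adherence, and each window's adherence shifting the score at its end by g SD. There were 400 runs per case. A pooled logit with cluster-robust standard errors stood in for the mixed model. Each cell gives the OR per SD and the share of runs with p < 0.05.

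| g (SD) | Same visit | Model 3, mean of months 3 and 6 | Model 3, mean of months 0, 3 and 6 |
|---|---|---|---|
| 0 | 1.00 (4%) | 1.00 (4%) | 1.00 (4%) |
| 0.1 | 1.11 (38%) | 1.09 (11%) | 1.08 (8%) |
| 0.2 | 1.23 (83%) | 1.17 (31%) | 1.13 (21%) |
| 0.3 | 1.36 (99%) | 1.26 (57%) | 1.20 (38%) |
| 0.5 | 1.68 (100%) | 1.49 (94%) | 1.38 (81%) |

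As a cross-check, two unit-variance normal distributions g apart imply OR = exp(g): exp(0.1) = 1.11, exp(0.2) = 1.22, exp(0.3) = 1.35, exp(0.5) = 1.65. A separate simulation with a random-intercept logit and an assumed 220 ED users gave a same-visit OR of 1.62 at g = 0.3. The two set-ups differ in sample size as well as estimator, but the table is not the upper end.

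**3. The same data with earlier scores.** The previous-wave score adjusted for previous adherence gave OR 1.00-1.01, significant in 2-6% of runs. For Model 3, the baseline score adjusted for baseline adherence gave OR 0.99-1.01 (4-7%). Unadjusted, the baseline score still gave 1.10 (14%) at g = 0.5, so the adjustment for prior adherence matters.

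**4. The opposite case.** Take no feedback and a true within-window OR of 1.5 per SD (220 users, three waves, 150 runs, all assumed). The same-visit mixed model recovers 1.48-1.53 (92-98% significant). With score autocorrelation of 0.3, 0.5 or 0.7, the lagged score gives 1.07, 1.18 or 1.31 (8%, 24%, 51%). Adding prior adherence gives 1.03, 1.11 or 1.20 (5%, 18%, 42%).

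**5. Precision lost by lagging.** The baseline outcome row drops out.
- Complete follow-up: √(3/2) = 1.22 for Model 1 and √(4/3) = 1.15 for Model 2.
- With the planned 15% loss applied at each follow-up visit: √(2.70/1.70) = 1.26 and √(3.55/2.55) = 1.18.

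These are row counts only. Rows without a prior visit, or with prior adherence missing because there was no sex or PrEP had not been started, add to the loss.

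**The case against.** The strongest reply is that the stated aim is association, which same-visit mixed models answer. That is right, and it is why the planned models should stay. It does not cover the independent-effects wording or the intended use for interventions.

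Second, nothing in the protocol shows that adherence feeds back on these scores, and every g above is assumed. This stands. A reader might infer that a score with no influence will appear as a strong factor; the documents support only that it can. At g = 0.1 the distortion is small.

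Third, a reader might infer that Model 3 openly uses scores taken after the whole outcome. It does not say so. It leaves the waves unnamed, and the mean may include scores that precede the windows.

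Fourth, lagging has a real price. Step 4 shows that a lagged model can miss a genuine factor. In Model 2 the 3-month score would be set against behaviour in months 5-6, two months before that window opens. This stands, and it rules out replacing the planned models with lagged ones.

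Fifth, the timing might be left to a separate analysis plan. But 3.8 carries that title, says the analyses will follow it, and states how the Model 3 covariates are built.

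**Conclusion.** The point holds in a limited form. No planned model sets an earlier psychosocial score against later adherence, so the plan cannot tell a factor for adherence from a consequence of it. With no true effect, an assumed feedback of 0.1-0.3 SD would give ORs of about 1.1-1.36 per SD for same-visit scores and about 1.1-1.3 in Model 3.

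This rests on same-visit pairing being intended beyond the baseline row, and on the psychosocial scales being repeated at follow-up. The reference to time-varying covariates implies the latter, but 3.5 lists questionnaire content only for baseline.

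A reader might also infer that the prospective design is lost. That goes too far: adherence prevalence by wave and the socio-demographic factors are unaffected, and sexual behaviours overlap the window rather than follow it. The sample size is not affected.

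**What to change.** Amend 3.8 and the limitations as follows.

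1. Keep Models 1 and 2. Label the same-visit psychosocial estimates as concurrent associations, and replace the term independent effects with adjusted associations.
2. Add a pre-specified lagged analysis, reported alongside, that pairs each follow-up outcome with the previous visit's score and adjusts for adherence at that visit. Model 1: baseline to month 3, month 3 to month 6. Model 2: baseline to month 1, month 1 to month 3, month 3 to month 6. State whether the random intercept is kept once prior adherence is a covariate; the check above used a pooled logit with cluster-robust standard errors.
3. In Model 3, name the waves averaged, leave out the 6-month score, and report a version with baseline psychosocial scores adjusted for baseline adherence. Only that version is wholly free of scores taken after part of the outcome.
4. Add reverse direction to the limitations, and describe a psychosocial factor as preceding adherence only where the lagged analysis supports it.

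The cost is wording and one further set of models. No new data are needed if the scales are repeated at follow-up, which 3.5 should confirm. Confidence intervals in the lagged analysis widen by about 22-26% for Model 1 and 15-18% for Model 2, or more, and effects confined to the window are understated.
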